### Objectives

a. To describe the uptake and use of *HeLP-Diabetes* by NHS services and patients.

b. To identify factors which inhibit or facilitate implementation.

c. To identify the resources needed for effective implementation.

d. To explore any effects of *HeLP-Diabetes* use on self-reported patient outcomes.

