### Outcomes

The study objectives will be addressed in the following ways.

a. To describe the uptake and use of *HeLP-Diabetes* by NHS services and patients.

The number of GP surgeries and diabetes clinics *HeLP-Diabetes* is offered to, and the numbers who take it up will be recorded. To describe the types of services that take up *HeLP-Diabetes* we will collect data including: the number of patients registered at the surgery or who attend the clinic (overall numbers and those with T2DM), socio demographics of the patient population and the number of staff. For GP surgeries we will also collect: Quality and Outcomes Framework (QOF) achievement and whether it is a training or non-training practice.

The number of patients who register on *HeLP-Diabetes* will be recorded and patient registration data will be used to describe the characteristics of patients who sign up. This data will include; year of birth, gender, ethnicity, the surgery or clinics they attend, duration of diabetes, existence of complications, how diabetes is currently managed; what help the patient would like with self-management, smoking status, internet access (home/public) and use of computer (basic/intermediate/advanced).

Data on *HeLP-Diabetes* use will be recorded automatically by the website software and Google Analytics and will include number of logins, length of time patients use *HeLP-Diabetes* per visit, pages that are visited and those that are not, and the tools, assessments, educational modules that are used and how often.

b. To identify factors which inhibit or facilitate implementation.

Semi-structured interviews will be conducted with key informants, both patients and health professionals and will be focussed on exploring the barriers and facilitators to implementation. The researcher will also keep detailed notes on the implementation process and document any challenges and successes.

c. To identify the resources needed for effective implementation.

A proforma will be used to collect quantitative data on the resources spent on implementing *HeLP-Diabetes*, which are predicted to be largely made up of staff and researcher time. Semi-structured interviews will be conducted with key informants, both patients and health professionals, to investigate the resources needed for effective implementation.

d. To explore the effects of *HeLP-Diabetes* on self-reported patient outcomes.

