Patient participants will be asked to complete two self-report measures. The first will be the Problem Areas in Diabetes (PAID) scale [22] which is a health related quality of life and emotional distress measure. It is comprised of 20 items focusing on areas that cause difficulty for people living with diabetes including; social situations, food, friends and family, diabetes treatment, emotions, relationships with healthcare professionals and social support. The second measure will be the Diabetes Management Self-Efficacy Scale (DMSES-UK) [23] which measures the individual’s efficacy expectations for engaging in 20 diabetes self-management activities, for example, taking daily exercise and keeping to a healthy eating plan when away from home. A sample size of 100 patients will detect a 3.5 point difference in the mean PAID score from baseline and a 9 point difference in the mean DMSES score from baseline. These calculations are based on 90% power (α = 0.05).

Additional self-report measures may be introduced to new cohorts of patients in order to test developing hypotheses generated by interviews with patients and staff. For example, if a theme emerges from the interviews suggesting that using *HeLP-Diabetes* may increase patients’ levels of physical activity, we may administer a physical activity self-report measure to a new cohort of patients at baseline, 3 months and 12 months to quantitatively explore this. Power and sample size will be calculated for each new measure prior to it being administered.

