### Anaylsis

The proportion of GP surgeries and clinics offered *HeLP-Diabetes* who adopt it, the number of patients who register on *HeLP-Diabetes*, the socio-demographic characteristics of the patients who take part in the evaluation study and the characteristics of the clinics and GP surgeries that adopt *HeLP-Diabetes* will be described using descriptive statistics. SPSS statistical software [24] will be used for coding and analysing these data. Descriptive statistics will also be used to explain how patients make use of *HeLP-Diabetes* including counts of pages accessed, number of logins, the times of use, the duration of use and the patterns of use by different users. This data will be recorded automatically by the website software. The time and other resources expended on implementing *HeLP-Diabetes* will be recorded on a proforma and these will be collated on a spread sheet and data described descriptively.

The cost of health professional input from the GP surgeries and clinics will be based on national average rates using Personal Social Services Research Unit estimates. Estimates of the additional time required from the general practice and clinic staff where *HeLP-Diabetes* is implemented will be calculated from responses in the qualitative interviews. Resources required in training individual patients to use *HeLP-Diabetes* will be estimated.

Participant scores on the PAID and DSMSE-UK scales will be compared statistically at the different time points using a repeated measures analysis of variance test using time as the independent variable. If a statistically significant effect is found post-hoc tests will be used to explore this further. Follow up PAID and DSMSE-UK scores will be adjusted for initial scores and other baseline covariates including age, gender, and duration of diabetes. Group effects including gender and age will be assessed using mixed-between within subjects analysis of variance.

With respondents’ consent, all semi-structured interviews will be audio-recorded, transcribed (and edited to ensure anonymity of respondent) and data will be subjected to formal analysis. Patient and staff interviews will be analysed inductively to identify themes and categories, a process of constant comparison will be used to establish analytical categories. Atlas. ti [25] data collation and management software will be used to aid data management and analysis.

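### Age is assessed as a group factor in a mixed ANOVA although it can stay continuous; banding it lowers the power to find an age effect

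*Protocol article*

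**What the plan says.** The analysis section of the protocol article describes three quantitative steps for the two self-report scales.

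- The main comparison over time is a "repeated measures analysis of variance test using time as the independent variable". Age plays no part in it.
- An adjusted analysis follows: "Follow up PAID and DSMSE-UK scores will be adjusted for initial scores and other baseline covariates including age, gender, and duration of diabetes". Age is a covariate here, and no grouping is mentioned.
- Subgroup-type effects come last: "Group effects including gender and age will be assessed using mixed-between within subjects analysis of variance".

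Under Outcomes, the data recorded when a patient registers include "year of birth, gender, ethnicity, the surgery or clinics they attend", so age is available to within a year. The matching objective is exploratory: "To explore any effects of *HeLP-Diabetes* use on self-reported patient outcomes".

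**The concern.** A mixed between-within ANOVA compares groups of patients across repeated measurements. Gender fits that design as it stands. Age fits only after it has been cut into bands, and the sentence names it beside gender as a group effect. Banding treats all patients within a band as having the same age and discards the differences between them. A gradient with age then becomes harder to detect.

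The authors single out age and gender for this assessment, so they evidently want an answer on age. With an internet-based programme, a reader will want to know whether change on the scales differs between younger and older patients. The sample was sized for overall change from baseline, not for an age effect, so there is no planned reserve of power to spend on grouping.

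**Working it through.** **Inputs from the article.** Under Outcomes: 100 patients, 90% power, α = 0.05, and detectable changes of 3.5 points (PAID) and 9 points (DMSES). The article gives no figure for an age effect and no banding scheme.

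**Assumptions.** Two-sided testing, a linear age effect, roughly normal age and equal-sized bands, with other cases shown as a range.

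**Step 1: the plan's own figure.** The article states that "A sample size of 100 patients will detect a 3.5 point difference in the mean PAID score from baseline". For a paired mean change, n = ((1.960 + 1.282) × SD / δ)². Solving for the SD of change at n = 100:

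- PAID: 3.5 × 10 / 3.2415 = 10.8
- DMSES: 9 × 10 / 3.2415 = 27.8

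The article prints no SD, so 100 can be neither confirmed nor refuted. It is used below only as the number of patients.

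**Step 2: information kept after banding.** For a linear effect the share kept is E = Var(band means) / Var(age).

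- Two equal bands, normal age: the band means are ±√(2/π), so E = 2/π = 0.637 and the loss is 36.3%.
- Three bands: the outer means are ±1.091, so E = (2/3) × 1.091² = 0.793 and the loss is 20.7%.
- Four bands: E = 0.861, loss 13.9%. Five bands: E = 0.897, loss 10.3%.

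The range under other conditions:

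- Uniform age: the loss is 1/k², that is 25.0%, 11.1%, 6.3% and 4.0% for two to five bands.
- Normal age, off-centre two-band split: the loss is 1 − φ(c)² / (p(1 − p)), that is 37.8% at 60/40, 42.4% at 70/30 and 51.0% at 80/20.

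**Step 3: power at N = 100.** Take one score per patient, such as the average over visits or the change to one follow-up. Let r be its correlation with age. Then R² = r²E, λ = N·R² / (1 − R²), and power comes from the noncentral F with k − 1 and N − k degrees of freedom (1 and 98 for continuous age).

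Continuous age has 80% power at r = 0.272 (λ = 8.01). This r is chosen only to set the benchmark; it is not a value from the article. The 90% benchmark is r = 0.311.

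| Age entered as | λ (80% benchmark) | Power (80% benchmark) | Power (90% benchmark) |
|---|---|---|---|
| continuous | 8.01 | 80% | 90% |
| 2 bands | 4.95 | 60% | 72% |
| 3 bands | 6.25 | 59% | 72% |
| 4 bands | 6.81 | 56% | 70% |
| 5 bands | 7.12 | 53% | 67% |

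More bands recover information, but the omnibus test spends it on extra degrees of freedom.

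**Step 4: a trend test on the bands.** With equally spaced scores and 1 and 98 degrees of freedom, the 80% benchmark falls to about 70% with three bands, 73% with four and 75% with five. The loss is smaller but does not vanish.

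The full age-by-time test over three time points has more numerator degrees of freedom under either approach and was not calculated here.

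**The case against.** The strongest reply is that the article fixes no banding scheme, so no single loss belongs to the plan. That stands. A reader might infer that the plan throws away about a third of the age information. That figure is right only for a split near the median of a roughly normal age distribution. Across the schemes in the working the loss runs from about 4% to 51%, and the power figures assume an omnibus test.

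Other tempting readings also go too far:

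- **The plan forces age into categories throughout.** It does not. Age is also a covariate in the adjusted analysis, and an ANOVA framework can carry a continuous covariate.
- **The two adjacent sentences conflict.** They do not. A variable may be a covariate in one analysis and a grouping in another.
- **The bands could be picked after the data are seen.** The article cannot support this as a fault. It condenses a fuller plan that is not shown, and cut-points are commonly left to that plan.

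It is also fair to say that a linear term wins only when the effect is roughly linear. If benefit turned at some age, bands could show what one slope would miss. The article suggests no such shape, and a simple check covers the risk.

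What survives is the choice of method itself: bands lose power against continuous age for a linear effect, even when they are specified in advance.

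**Conclusion.** The point holds as a minor improvement. The article's stated method for age ordinarily means bands, the data allow age to stay continuous, and banding lowers power for a linear age effect under every scheme tried.

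With normal age and equal bands, the information loss is about 36%, 21% or 14% for two, three or four bands. A benchmark of 80% power falls to about 53–60% with an omnibus test, or to about 70–75% with a trend test on three to five bands. These sizes depend on the assumed age distribution, on linearity and on the banding scheme; none of them is a figure in the article.

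The effect is confined to a secondary analysis under an exploratory objective. The sample size and the main test of time do not change.

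**What to change.** Reword the one sentence. Test age as a continuous age-by-time term in the repeated-measures model, keep gender as a between-subjects factor, and use age bands only for descriptive tables or plots. Add a check for curvature, for example a quadratic age term with its interaction with time, since a single slope can miss a non-linear pattern.

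The cost is one sentence of analysis wording and a small amount of modelling. It needs no new data, visits or patients.

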## Discussion

This study will explore what happens when a new internet-based self-management intervention for patients with T2DM is introduced into existing NHS services. Quantitative data will describe the use of *HeLP-Diabetes* by NHS organisations and patients and allow us to determine the socio-demographic characteristics of users and the type of service that take up *HeLP-Diabetes.* We will determine the cost of implementation and the resources needed for successful implementation. Qualitative data will allow us to understand the implementation process and explore barriers and facilitators to implementing *HeLP-Diabetes* into existing services. We will explore the possible impact of *HeLP-Diabetes* use on patient-reported health-related quality of life, emotional wellbeing and self-efficacy to self-manage T2DM. This study will produce findings useful for those embarking on the implementation of an internet based resource within the NHS.

Translating research into routine clinical practice is often a difficult task. Implementation research is often focused on the early stages of the implementation process [26] however, there is also a need to examine later stages of implementation, including the integration of innovations into the norms and practices of organisations. Exploring the implementation of *HeLP-Diabetes* with a longitudinal study over 30 months will provide an opportunity to examine issues and challenges that emerge during the many stages of implementation including the less researched later stages.

There are several strengths of the design of this study. Data on the implementation of *HeLP-Diabetes* will be collected from staff across diabetes services and from a range of staff within these services. This will include both management and front-line staff as these groups may have very different viewpoints and perceptions of organisational change [27].

The iterative design of the study will allow for the implementation plan to change and develop in line with experiential learning and feedback from those involved in the implementation process. This is important in creating a final implementation procedure that is fit for purpose and effective. The mixed method design will aid the process of exploring the impact of *HeLP-Diabetes* on patient outcomes. By conducting interviews with patients throughout the study, emerging themes pertaining to the possible benefits of *HeLP-Diabetes* can be explored in greater detail with further interviews. We can also test emerging hypotheses about the mechanisms of action borne out of the interviews by administering further self-report measures to new cohorts of patients at baseline, 3 month and 12 month follow up.

The study faces some potential methodological and practical challenges. The study is limited to two inner London boroughs; the patient population and the services within which we are seeking to implement *HeLP-Diabetes* which may limit the generalizability of findings. In terms of studying the patient experience of *HeLP-Diabetes*, only the views of those patients who agree to take part in the research evaluation will be included. The views of those who don’t use *HeLP-Diabetes* and those using it but not taking part in the research study will not be represented.

The need for patients to attend a training appointment to use *HeLP-Diabetes* may be a potential bottle-neck to uptake. However, we believe that this tailored appointment will ensure that patients can use *HeLP-Diabetes* optimally. A research question to be addressed within this study is what is the most effective and viable way to ensure *HeLP-Diabetes* is a useful, effective and sustainable resource for patients and the evaluation of this training appointment will be central to that.

It is likely that internet-based health interventions will become increasingly widespread, not just for diabetes but for other long term physical conditions and mental health problems. There is a need to understand the implementation process of these interventions including the uptake by health organisations and patients, the facilitators and barriers to use and the resources needed for successful implementation and normalization. This study will offer a contribution to this.

## Abbreviations

CCG: Clinical Commissioning Group; DMSES-UK: Diabetes management self efficacy scale; GP: General practice; NHS: National Health Service; NICE: National Institute for Health and Clinical Excellence; NPT: Normalisation process theory; PAID: Problem Areas in Diabetes; T2DM: Type 2 diabetes mellitus
